**Methods/Design:**

This study is a cluster randomised trial, with practices allocated to one of three groups 1) Quit with Practice Nurse 2) Quitline referral 3) GP usual care. PNs from practices randomised to the intervention group will receive a training course in smoking cessation followed by access to mentoring. GPs from practices randomised to the Quitline referral group will receive information about the study and the process of written referral and GPs in the usual care group will receive information about the study. Eligible patients are those aged 18 and over presenting to their GP who are daily or weekly smokers and who are able to give informed consent. Patients on low incomes in all three groups will be able to access free nicotine patches.

Primary outcomes are sustained abstinence and point prevalence abstinence at the three month and 12 month follow-up points; and incremental cost effectiveness ratios at 12 months. Process evaluation on the reach and acceptability of the intervention approached will be collected through Computer Assisted Telephone Interviews (CATI) with patients and semi-structured interviews with PNs and GPs.

The primary analysis will be by intention to treat. Cessation outcomes will be compared between the three arms at three months and 12 month follow-up using multiple logistic regression. The incremental cost effectiveness ratios will be estimated for the 12 month quit rate for the intervention groups compared to usual care and to each other. Analysis of qualitative data on process outcomes will be based on thematic analysis.

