## Background

Tobacco remains the most common preventable cause of death in the world today. The World Health Organization estimates that tobacco killed 5.4 million people globally in 2008 and on current trend this will rise to 8 million deaths per year by 2030 with more than 80% of deaths occurring in the developing world [1]. Despite reduction in prevalence of smoking in the Australian population, tobacco use and dependence remains the risk factors associated with the greatest disease burden, accounting for 9.5% of the total burden in men and 6% in women [2]. More than one in six Australians continue to smoke each day, and tobacco smoking is responsible for the premature deaths of about 16,000 Australians each year [3]. Less than 10% of Australian smokers consistently deny any interest in quitting and approximately 40% report attempting to quit in the previous year [4]. Unfortunately unaided quit attempts have a low success rate of only 3-5% [5].

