#### Primary outcomes

Uptake of the intervention in each group and characteristics of patients - age, sex, language spoken at home, ethnicity, education levels, occupation, smoking history, level of smoking and nicotine dependence.

Smoking cessation rates: sustained abstinence defined as patients reporting abstinence of ≥ one month at the three month follow-up and ≥ 10 months at the 12 month follow-up; and point prevalence abstinence defined as ≥ seven days of sustained abstinence at the three month and 12 month follow-up points. Validation of smoking cessation will not be undertaken as reviews confirm the accuracy of self-report measures, and conclude that validation is unnecessary in trials where there is no strong association between the interviewer and respondent [43]. Number and duration of quit attempts will be a further outcome measure as it is known that the key effect of advice from a health professional is to encourage the smoker to try to quit [10,11].

Health economic outcomes: the economic evaluation will compare the flexible support intervention 'Quit with Practice Nurse' and the 'Quitline referral intervention' with standard 'in practice management by the GP' (control group.) Cost analysis will be from the perspective of the health care sector and include direct costs of the intervention, including for recruitment, and for the intervention (GP costs, practice nurse costs, nurse training costs, telephone counseling costs, pharmaceutical costs, and overheads such as room rents).

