#### Health economic analysis

The study will estimate incremental cost effectiveness ratios (ICER) of cost per quitter for brief advice and referral to Quitline, and with the flexible support intervention, compared to standard GP care. The ICER will be estimated for the 12 month quit rate for the intervention, less an unaided/natural quit rate. Adjustments to effect sizes will also be made for long term relapse rate among the 12 month quitters.

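### The ICER rule subtracts an unspecified natural quit rate from the intervention although the comparator is a randomised usual-care arm that already contains background quitting

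*Protocol article*

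**What the plan says.** The protocol article describes the incremental cost-effectiveness ratio (ICER) in three places.

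- **Health economic analysis.** The first sentence announces cost per quitter for Quitline referral "and with the flexible support intervention, compared to standard GP care". The second gives the effect measure: "The ICER will be estimated for the 12 month quit rate for the intervention, less an unaided/natural quit rate". The third adds: "Adjustments to effect sizes will also be made for long term relapse rate among the 12 month quitters".
- **Primary outcomes**, health economic paragraph. Both interventions are compared "with standard 'in practice management by the GP' (control group"). No natural quit rate is mentioned.
- **Abstract, Methods/Design.** ICERs at 12 months are listed among the primary outcomes and are to be estimated "for the 12 month quit rate for the intervention groups compared to usual care and to each other". Again no natural quit rate is mentioned.

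The article gives the natural rate no value, definition or source for this use, and does not say that it is also subtracted in the control arm. The nearest figure is in the Background: "Unfortunately unaided quit attempts have a low success rate of only 3-5"%. The economic section does not refer to it.

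**The concern.** Usual care is randomised and followed up in the same way as the other two arms. Its 12-month quit rate therefore already measures what happens without the new support, including spontaneous quitting. The difference from that arm is the incremental effect, and no further correction for background quitting is needed.

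The second sentence of the section nevertheless takes a natural rate off the intervention's quit rate. It can be read in three ways:

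- **Double subtraction.** The natural rate is removed from the intervention and the result is then compared with usual care. Background quitting comes off twice.
- **Replacement.** The natural rate stands in for the usual-care rate. The effect side then loses the randomised comparison. If costs remain incremental to GP care, numerator and denominator have different comparators.
- **Subtraction from every arm.** The constant cancels in each contrast and does nothing.

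The ICER is listed as a primary outcome, and the third study objective asks whether any extra cost of the nurse model is justified by its results. Under the first two readings the answer depends on a constant that is not fixed in advance.

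**Working it through.** **Inputs.** From Sample size: planned 12-month sustained abstinence of 2.6% (usual care), 6.5% (Quitline referral) and 12% (practice nurse). The article states no ICER, so there is no economic figure to reproduce. The planning rates can be checked through the sample size. A two-sided 5% test with 80% power and continuity correction gives 471 per group for 6.5% v 12% and 140 for 2.6% v 12%, as stated. The design effect is 1 + 24 × 0.013 = 1.312; 471 × 1.31 = 617 per arm, and 3 × 617 = 1851, also as stated.

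**Natural rate *x* (assumption).** The article sets no value, so a range is needed. The upper part is the Background's 3-5%, which is success per unaided attempt, whereas the trial's rates are per enrolled smoker. For a rough per-smoker value, the Background says about 40% of smokers report an attempt in the previous year. Assuming one unaided attempt each, 0.40 × 3% = 1.2% and 0.40 × 5% = 2.0%. The range used is therefore 1.2% to 5%.

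**Formulas**, with *p* the intervention rate and 2.6% the usual-care rate:

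- Randomised contrast: *p* − 2.6. Nurse 12 − 2.6 = 9.4 points; Quitline 6.5 − 2.6 = 3.9 points.
- Double subtraction: *p* − *x* − 2.6.
- Replacement: *p* − *x*.
- Subtraction from every arm: (*p* − *x*) − (2.6 − *x*) = *p* − 2.6, unchanged.

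The ICER multiplier is the randomised contrast divided by the distorted one, holding incremental cost fixed. Each cell shows points, with the multiplier in brackets.

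| *x* | Double, nurse | Double, Quitline | Replace, nurse | Replace, Quitline |
|---|---|---|---|---|
| 1.2% | 8.2 (1.15) | 2.7 (1.44) | 10.8 (0.87) | 5.3 (0.74) |
| 2.0% | 7.4 (1.27) | 1.9 (2.05) | 10.0 (0.94) | 4.5 (0.87) |
| 2.6% | 6.8 (1.38) | 1.3 (3.00) | 9.4 (1.00) | 3.9 (1.00) |
| 3% | 6.4 (1.47) | 0.9 (4.33) | 9.0 (1.04) | 3.5 (1.11) |
| 4% | 5.4 (1.74) | -0.1 (negative) | 8.0 (1.18) | 2.5 (1.56) |
| 5% | 4.4 (2.14) | -1.1 (negative) | 7.0 (1.34) | 1.5 (2.60) |

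**What the table shows.**

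- Double subtraction always inflates the ICER, and more for Quitline than for the nurse model because the same constant comes off a smaller effect. Quitline's increment turns negative only when *x* exceeds 3.9%.
- Replacement understates the ICER when *x* is below 2.6% and overstates it when *x* is above. Quitline is again moved proportionally more, so the ranking of the two models is affected as well as the level.

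**The case against.** The strongest reply is that the sentence is loose, not wrong. The sentence before it, the Primary outcomes section and the abstract all name usual care as the comparator. An economist might form a net quit rate for every arm and then contrast the arms, which is harmless. Modelling detail is also commonly left to a fuller document. Part of this stands: nothing in the article proves that background quitting will be subtracted twice. But the harmless reading is not stated, since the text applies the subtraction to the intervention only, and under that reading the step has no purpose. This is a stated rule that conflicts with the stated comparator, not an omitted detail.

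A reader might also draw four stronger inferences that the article does not support:

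- *That 3-5% will be the natural rate, so every ICER is inflated.* The economic section does not cite that figure, and its denominator is quit attempts, not enrolled smokers. At 1.2% to 2.0%, replacement would make the ICER too low.
- *That Quitline will appear to yield fewer quitters than usual care.* This requires double subtraction and a natural rate above 3.9%, which is higher than the planned usual-care rate itself.
- *That the economic section rules out an ICER of nurse against Quitline.* It names only the contrasts with GP care but contains no limiting word, and the abstract promises the third contrast.
- *That the long-term relapse adjustment is faulty.* No defect in it is shown. It is a separate step and does not settle the comparator question.

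**Conclusion.** The point holds as a conflict between the named comparator and the stated effect rule for an outcome that the abstract lists as primary. Followed literally, the rule double-counts background quitting or drops the randomised control from the effect side; the one harmless reading is unstated and makes the subtraction redundant.

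The size cannot be fixed because the constant is not fixed. The tabulated range is an illustration that rests on the planning rates, an assumed natural rate of 1.2% to 5% and unchanged incremental cost. What does not depend on the chosen value is that a usual-care arm makes the external rate unnecessary, and that leaving it open lets an unspecified number move a primary economic result.

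Randomisation, sample size, data collection and the cessation comparison are not affected.

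**What to change.** Replace the second sentence of Health economic analysis with wording such as: *The incremental effect is the difference between randomised arms in the 12-month quit rate.* State the three contrasts there: nurse v usual care, Quitline v usual care and, as the abstract has it, nurse v Quitline.

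Add that any long-term relapse adjustment applies equally to the 12-month quitters of all arms. If a natural quit rate is still wanted, confine it to a sensitivity or modelling analysis labelled as such, with its value, source and denominator (per smoker or per attempt) stated beforehand.

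The cost is one paragraph of protocol or economic-plan wording, settled before the economic analysis. Quit status and costs are already collected, so no new data are needed.

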#### Analysis of qualitative data on process outcomes

Analysis will be based on thematic analysis. Our aim is to identify common themes and issues about barriers and facilitators to the uptake of the intervention from the perspective of both patients and providers. This will allow a richer understanding of the experiences of participants in the study and maximise our capacity to provide meaningful answers to our research questions [44].

#### Sample size

The observed 12 month sustained abstinence outcomes of GP usual care and Quitline referral in Borland et al.'s study in Victoria were 2.6% and 6.5% respectively [16]. The sustained abstinence at six months in a pilot study of practice nurse support was 16%. Assuming this drops to 12% at 12 months we have calculated power to detect a 5.5% difference in sustained abstinence quit rates between 'Quit with Practice Nurse' intervention versus the referral intervention and a 9.4% difference between 'Quit with Practice Nurse' intervention and the usual care control group at one year follow up with 80% power at the 5% significance level. Before adjustment for clustering this requires 471 patients per group to detect the 5.5% difference and 140 per group to detect the 9.4% difference (calculations using STATA software). To adjust for clustering the intracluster correlation coefficient observed by Lennox et al. in a smoking cessation trial in general practice has been used. The intracluster correlation coefficient observed in this study was 0.013 [45]. The resulting design effect = [1+ (size of cluster-1) × intracluster correlation]. In this study we plan to recruit 25 patients per practice so the design effect is 1.31 so the number per arm is 471 × 1.31 = 617 giving a total sample size of 1851. To enroll these participants we will recruit 90 general practices and 2250 patients across New South Wales and Victorian study locations (to allow for approximately 10% drop out rate of practices) and randomise 30 practices to each arm of the study.

#### Ethics Approval

The study has received ethics approval from the University of New South Wales, University of Melbourne and University of Western Sydney Human Research Ethics Committees.

#### Trial Registration

Australian New Zealand Clinical Trials Registry (ANZCTR). Number: ACTRN12609001040257.

## Discussion

This project will test an approach to supporting smoking cessation in general practice based on partnership between the practice nurse, GP and patient to support quitting. This is a new approach in Australia which has not had a system to provide face to face quitting support from specifically trained health professionals in a way that is accessible for most of the population. If successful it would have major benefits for addressing smoking which remains Australia's most important cause of preventable death and disease. The project is highly relevant with current policy direction in developing practice nurse roles and expanding access to Medicare rebates for services provided by practice nurses. Trials of actual interventions involving practice nurses have been identified as an important step in advancing the practice nurse role [22] and this study will provide key evidence to inform this development.

## Abbreviations

GP: General Practitioner; CA: TIComputer Assisted Telephone Interviews; CALD: Culturally and Linguistically Diverse; LYS: Life Years Saved; CONSORT: CONsolidated Standards Of Reporting Trials; ICER: Incremental Cost Effectiveness Ratios; STATA: Portmanteau of the words "statistics" and "data"
